### Asking for Attribution in Intersectional Discrimination Measures

To date, intercategorical, intersectional discrimination studies have adapted extant measures to permit multiple attributions [31-36]. Research has highlighted attributional ambiguity among individuals situated at the intersection of marginalized SSP [54-56]. Allowing multiple attributions may not reduce cognitive burden or improve measurement validity; for example, conceptual slippage between SSPs may make participant selections arbitrary [56]. Options for quantitatively modeling attributions are limited because they are not tied to frequencies; this has resulted in analyses that either dichotomize discrimination or count attributions [31-36,57], representing losses of information on dose-response relationships [58] and on the complexity of experiences at particular intersections [26]. Therefore, the InDI was designed to be attribution free. This decision rests on a lack of evidence that the health impacts of discrimination depend on attribution. Some researchers have argued that a different construct underlies measures of discrimination that include attributions to perceived discrimination compared with those that do not [59], but no study has empirically tested the validity of this claim. Indeed, a 2015 review noted that the few studies comparing attributed and unattributed (racial and ethnic) discrimination measures have compared *apples and oranges* (ie, measures that reflect different constructs); the authors called for direct comparisons, including cognitive interviewing [18]. Further, some research participants reported the ability to unambiguously attribute discrimination to one or more SSP, and health disparities researchers remain interested in the burden and consequences of specific discrimination types [47,56]. Thus, we will conduct an evaluation inclusive of participant perspectives, examination of the degree to which SSP and attributions overlap, and direct comparison of correlations with health outcomes.

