### Objectives

The primary aims of the study are to (1) assess the content and wording of the InDI measures (InDI-A, InDI-D, InDI-M) in English and Spanish; (2) evaluate the InDI measures’ configural, metric, and scalar structures, as well as their measurement equivalence across language and intersecting SSP; and (3) determine whether attributions should be included in the InDI measures.

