#### Intersectional Discrimination Index

All Spanish-language participants will receive the unattributed InDI (Multimedia Appendix 1), with potential modifications based on cognitive interview findings. For the English survey, we will use the block-randomization feature in Qualtrics to implement a split-ballot design: 1000 participants will receive each of the unattributed, item-level attributed, or overall attributed versions of the InDI.

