#### Health Outcomes

To permit psychometric evaluation of these novel instruments (aim 2) and comparisons between attribution methods (aim 3), analyses in the current proposal will focus on two of the most well-established health consequences of perceived discrimination: psychological distress and self-rated general health [15]. Psychological distress will be measured using the 6-item K6 measure developed by Kessler et al [66]. The K6 was developed to estimate the prevalence of serious mental illness and has shown good sensitivity and excellent specificity in US population samples when dichotomized at a score of 13/24 or above and compared with Diagnostic and Statistical Manual of Mental Disorders-IV diagnoses via structured clinical interviews [66,67]. Self-rated general health, a robust predictor of morbidity and mortality [68], will be assessed using a standard question from the Behavioral Risk Factor Surveillance System and other federal surveys (“Would you say in general that your health is—excellent, very good, good, fair, or poor?”). To facilitate secondary analyses of these data focused on a wider range of health outcomes, the survey will also collect data on substance use (nicotine, alcohol, and illicit drugs), hypertension, and diabetes.

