We will use mCFA to determine whether the configural, metric, and scalar structures of the InDI measures are equivalent across (1) language (English vs Spanish) and (2) the 12 intersectional race and ethnicity*SGM*gender sample strata. Achieving equivalence across all these scale structures is necessary for the InDI measures to generate meaningful cross-group comparisons. After estimating the baseline models for each group, we will test configural equivalence across language and intersectional strata. We will then assess the metric equivalence of the scales by examining whether factor loadings vary across these groups by comparing the fit of the metric models with those of the configural models. To assess scalar equivalence, item thresholds will be tested for their equivalence among the same groups. Formal comparisons will be carried out by comparing the fit of the scalar models with those of the metric models. To compare less (eg, configural) and more restrictive (eg, metric and scalar) models, we will use a reduction ≥0.002 in the value of the comparative fit index as an unbiased indication of lack of equivalence, given the sensitivity of *P* values to large sample sizes [75]. We will also assess the partial invariance of the InDI measures. If needed (eg, because of numerous large modification indices), the alignment method will be used as an alternative to assess measurement equivalence [76].

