##### Quantitative Analysis

As a first step, we will compare discrimination burden (mean or median score on each of the InDI-A, InDI-D, and InDI-M) across the three conditions for each measure (unattributed, item-level attribution, and overall attribution) to determine whether the presence of attributions influences reporting. We will use appropriate parametric and nonparametric statistics (eg, chi-square and Mann-Whitney U test) to test for statistically significant differences between conditions. Next, we will estimate concordance between intersectional SSPs and discrimination attributions to determine the extent to which attributions align with SSPs. Among those reporting any discrimination in both the item-level and overall attribution conditions, we will calculate the proportion of (1) Black or Latino/a/x individuals who report racial and/or ethnic discrimination, (2) SGM individuals who report sexuality and/or gender identity–related discrimination, and (3) Black or Latino/a/x SGM who report both types of discrimination. In the item-level attribution condition, we will further calculate the proportion of items for which the aforementioned groups endorsed the respective attributions.

Finally, we will compare the magnitude of effect on psychological distress (continuous) and fair or poor (vs good or excellent) self-rated general health of reporting each discrimination type (InDI-A, InDI-D, and InDI-M), (1) based on sexuality and/or gender identity, (2) based on race and/or ethnicity, or (3) based on both (1) and (2). Using data from the attributed conditions, we will fit linear regression models to separately estimate the association between a categorical indicator of discrimination attributions (race and/or ethnicity, sexuality and/or gender, both, or other attributions only) and psychological distress, adjusting for total discrimination burden. These analyses will be conducted separately among Black and Latino/a/x SGM reporting any discrimination for each measure (InDI-A, InDI-D, and InDI-M). Parallel analyses focused on attributions to race and/or ethnicity, gender, both, or other attributions will be conducted among Black and Latino/a/x women. For self-rated health, we will use a similar approach with logistic regression.

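### Across the three randomised InDI versions only score level is compared; measurement structure and the association with health are not, although the article raises both questions

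*Protocol article*

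**What the plan says.** **Purpose.** In the Protocol article, Objectives, Aim 3 is to "determine whether attributions should be included in the InDI measures". The Introduction's section on asking for attribution reports a view in the literature that "a different construct underlies measures of discrimination that include attributions to perceived discrimination compared with those that do not", and adds "but no study has empirically tested the validity of this claim". The same section ends with a commitment to a "direct comparison of correlations with health outcomes". Under Health Outcomes, distress and self-rated health are said to serve "comparisons between attribution methods (aim 3") as well as the psychometric work of Aim 2.

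**Design.** Under Intersectional Discrimination Index in the Methods, the English survey is a split ballot: "1000 participants will receive each of the unattributed, item-level attributed, or overall attributed versions of the InDI". All Spanish respondents receive the unattributed form.

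**Analysis.** The Quantitative Analysis section of Aim 3 has three steps.

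1. Mean or median burden on each measure is compared across the three versions.
2. Concordance between social position and attribution is estimated in the attributed versions.
3. Health models are fitted: "Using data from the attributed conditions, we will fit linear regression models to separately estimate the association between a categorical indicator of discrimination attributions". They are limited to Black and Latino/a/x SGM respondents who report discrimination, with a parallel set in Black and Latino/a/x women, and they carry total burden as a covariate.

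In Aim 2, multigroup CFA is grouped by language and by the 12 quota strata. The MIMIC covariates are six social-position variables. Version appears in neither.

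**The concern.** Score level is only one of the ways in which two versions of an instrument can differ. Equal means are compatible with different loadings, different thresholds and different associations with health. Unequal means show that asking for reasons shifts reporting, but not which version measures better. The construct question that the Introduction raises therefore needs a comparison of measurement structure between versions. The promised health comparison, on its natural reading alongside Health Outcomes, needs the InDI–health association to be estimated in each version.

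The split ballot is well suited to both. Because version is randomised, underlying experience of discrimination is the same on average in the three arms. A difference between arms in structure or slope can then be put down to the version. The planned health models contrast attribution categories that respondents choose themselves, so they do not use that randomisation.

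There is also a consequence for Aim 2. If the stratum analysis pools versions, it assumes without a check that they are interchangeable. If the language analysis sets Spanish (all unattributed) against pooled English, language is mixed with version. The article does not say which English respondents enter these analyses.

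**Working it through.** **1. The plan's own figures.** From Participants and Sample Size: 12 strata × 250 = 3000. From the split-ballot description: 3000 / 3 = 1000 per version. Both reproduce. The minimum of 200 per group comes from a cited simulation and cannot be re-derived from the article.

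**2. What each stated analysis compares.**

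| Analysis | Versions used | Contrast |
|---|---|---|
| Mean or median burden | all three | score level between versions |
| Concordance | two attributed | social position against attribution |
| Distress and self-rated health models | two attributed | attribution categories at equal burden |
| Multigroup CFA | not stated | language; 12 strata |
| MIMIC | not stated | six social-position covariates |
| Mixed-methods integration | qualitative with quantitative | no cross-version test added |

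No row compares factor structure, loadings or thresholds between versions, or the InDI–health association between versions.

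**3. Reach of the health models.** Black and Latino/a/x SGM respondents in English: 2 × 500 = 1000. Two of the three versions: 1000 × 2/3 ≈ 667 of 3000, before restriction to those reporting discrimination. None comes from the unattributed version.

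**4. Pooling.** A stratum of 250 holds on average 250 / 3 ≈ 83 respondents per version. The stratum size therefore exceeds the plan's minimum of 200 only if versions are pooled.

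**5. What the sample could detect.** The article gives no alpha, power or effect size for Aim 3. I assume two-sided 0.05 and 80% power, so the multiplier is 1.96 + 0.84 = 2.80.

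- Multigroup CFA by version: 1000 / 200 = 5 times the plan's minimum per group.
- Mean scores, one pair of versions: 2.80 × √(2/1000) = 0.125 SD.
- Correlations, one pair: Fisher-z difference 2.80 × √(2/997) = 0.125.
- Correlations, unattributed against both attributed versions pooled: 2.80 × √(1/997 + 1/1997) = 0.109.
- Correlations, one pair with Bonferroni for three pairs: 0.145.

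On the correlation scale, for one pair:

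| r in one version | Detectable r in the other, unadjusted | With Bonferroni |
|---|---|---|
| 0.20 | 0.32 or 0.08 | 0.33 or 0.06 |
| 0.30 | 0.41 or 0.18 | 0.43 or 0.16 |
| 0.50 | 0.59 or 0.40 | 0.60 or 0.38 |

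The values of r are assumed, to show the range. The figures concern unadjusted correlations. They carry over to slopes only if scores and outcomes have similar spread in each version, and they do not cover the logistic models.

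**The case against.** The best defence starts from the reason given for leaving attributions out: there is no evidence that the health effect of discrimination depends on attribution. The planned regressions address that premise by comparing attribution categories at equal burden. Only someone who was asked for reasons can contribute, so leaving the unattributed arm out of that model is a logical necessity. The promise in the Introduction can also be read narrowly, as a comparison of health associations by type of attribution, and the planned analyses follow the order of that closing list. This stands as a defence of the existing models. It does not fill the gap, because those models cannot compare an attributed with an unattributed instrument, and Health Outcomes speaks of comparing attribution methods.

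A reader might infer more than the article supports, in three ways.

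- *That Aim 3's central question goes untested.* It does not. Reporting shift, concordance, health effects by attribution type, cognitive probing and participants' views all bear on it.
- *That the randomised contrast is not analysed.* It is, for score level on all three measures.
- *That unattributed respondents enter no health analysis at all.* Health Outcomes also assigns these outcomes to Aim 2 without excluding any version. What can be said is that no stated model relates score to health by version.

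Finally, a steeper InDI–distress slope in one version need not mean better validity, since asking for reasons could itself raise shared reporting variance. That stands, and it limits the weight the added models should carry.

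Article condensation does not explain the gap: the article spells out arms, exposure, outcomes, population and adjustment for the Aim 3 models.

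**Conclusion.** The concern holds in a limited form. Across the randomised versions the plan compares score level only. It states no comparison of measurement structure or of the InDI–health association, although the Introduction raises the first question and, with Health Outcomes, points to the second. The existing Aim 3 analyses are valid and should stay. As planned, they cannot show whether attributed and unattributed versions measure the same construct or relate equally to health.

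No further recruitment is needed. The detectable gap of about 0.125 in Fisher z per pair is moderate, so smaller differences could be missed. It rests on the assumed alpha and power and makes no allowance for multiplicity. The case for multigroup CFA by version also assumes that the item wording is common to the three versions; the appendix with the test measures is not shown.

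**What to change.** In the 3000 English respondents, add to Aim 3, before the data are examined:

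1. **Multigroup CFA with version as the grouping factor**, for each of InDI-A, InDI-D and InDI-M, using the plan's own criterion of a fall of at least 0.002 in the comparative fit index. Run it before interpreting mean differences, and before pooling versions in the stratum and language analyses. State which English respondents enter the language comparison.
2. **Health models by version**: K6 (linear) and fair or poor self-rated health (logistic) on InDI score, version and score × version, adjusted for the 12 strata, for each measure. Report the differences in slope between versions with 95% confidence intervals.

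Read both alongside concordance, the attribution-category models and the qualitative findings, not as the sole or main criterion. Do not take a non-significant interaction as equivalence; judge the interval.

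Also reconcile the Introduction and Health Outcomes with the Aim 3 analysis, so that it is clear which health comparison is meant.

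The cost is a few extra models on data already planned, and some multiplicity: 3 measures × 2 outcomes = 6 models, each with 3 pairwise slope differences, or 18 contrasts. A single joint test of the interaction in each model would keep that to 6.

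### The Aim 3 health models compare attribution groups at equal burden, so they cannot show whether the relation between discrimination burden and health differs by attribution

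*Protocol article*

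**What the plan says.** In the Introduction (Asking for Attribution in Intersectional Discrimination Measures), the article explains why the InDI leaves attributions out: "This decision rests on a lack of evidence that the health impacts of discrimination depend on attribution". For the present study it announces, among other elements, a "direct comparison of correlations with health outcomes".

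Under Aim 3, Quantitative Analysis, the health part sets out to "compare the magnitude of effect on psychological distress (continuous) and fair or poor (vs good or excellent) self-rated general health of reporting each discrimination type", according to whether the mistreatment was put down to sexuality or gender identity, to race or ethnicity, or to both. The method follows:

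- Model: "Using data from the attributed conditions, we will fit linear regression models", which relate these two quantities: "a categorical indicator of discrimination attributions (race and/or ethnicity, sexuality and/or gender, both, or other attributions only) and psychological distress, adjusting for total discrimination burden".
- Population: "These analyses will be conducted separately among Black and Latino/a/x SGM reporting any discrimination for each measure". A parallel set is planned for Black and Latino/a/x women.
- Binary outcome: "For self-rated health, we will use a similar approach with logistic regression".

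The stated model has no term that lets the association with burden vary by attribution category.

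**The concern.** Whether an impact depends on attribution is a question of effect modification: does distress rise with discrimination at the same rate whatever the attributed reason? The stated model holds that rate equal across the four categories and asks whether the parallel lines sit at different heights. Everyone in the analysis reports discrimination, so no unexposed group shows whether a difference in height was there without it.

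A reader could then go wrong in two ways. A constant gap (for example, people who name both reasons being more distressed at every level of burden) could be reported as a larger effect of that kind of discrimination. Or a true difference in slope could produce no signal and be reported as evidence that attribution does not matter. These are the only planned models that relate attribution to health, so their wording carries into what Aim 3 can conclude.

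**Working it through.** **1. Sizes from the article.** Sample Size: 3 racial and ethnic groups × 2 SGM levels × 2 genders × 250 = 3000, which reproduces the stated English total. Black and Latino/a/x SGM number 2 × 500 = 1000. The split ballot gives 1000 respondents to each of three versions, so 2/3 receive an attributed version: 1000 × 2/3 ≈ 667, or 500 × 2/3 ≈ 333 if each group is modelled alone. The set for women has the same size (2 groups × 2 SGM levels × 250 = 1000, then 2/3). These are upper bounds, because only those reporting discrimination are analysed.

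**2. What the coefficient measures.** Suppose mean distress in category g is a_g + b_g·x, with x the burden, and that burden has the same distribution in every category. The planned model fits a common slope, and its coefficient for g against the reference r is then

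(a_g − a_r) + (b_g − b_r) × mean burden.

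Gap and slope difference enter as one sum. Different truths can give the same coefficient, and the two parts can cancel.

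**3. Simulation of the linear model.** The article gives none of these inputs, so all are assumptions: residual SD 5 distress (K6) points; burden scaled 0–1 with mean 0.5 (Beta(2,2)); common slope 6; category shares 30/25/30/15%; alpha 0.05; 2000 replicates. One category (25% share) differs from the rest. Both tests are 3-df F tests.

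| Truth for that category | Coefficient by formula | Planned test rejects, n=667 / 333 | Product-term test rejects, n=667 / 333 |
|---|---|---|---|
| Constant gap 1, equal slopes | 1.0 | 43% / 23% | 5% / 5% |
| Constant gap 1.5 | 1.5 | 80% / 47% | 5% / 5% |
| Constant gap 2 | 2.0 | 97% / 76% | 5% / 5% |
| Slope +3, crossing at mean burden | −1.5 + 3 × 0.5 = 0 | 5% / 5% | 18% / 12% |
| Slope +6, crossing at mean burden | −3 + 6 × 0.5 = 0 | 5% / 4% | 70% / 38% |
| Slope +3, meeting at zero burden | 3 × 0.5 = 1.5 | 80% / 49% | 20% / 13% |
| Slope +4, meeting at zero burden | 4 × 0.5 = 2.0 | 97% / 73% | 37% / 20% |
| Slope +6, meeting at zero burden | 6 × 0.5 = 3.0 | 100% / 98% | 70% / 39% |

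Simulated mean coefficients at n=667 agreed with the formula (for example 1.51 for the gap of 1.5 and 1.51 for slope +3 from zero). The planned test gives those two rows the same result.

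**4. Other assumptions.** A second set used a standardised scale: skewed burden, slope 0.4 per SD of burden, shares 25/25/35/15%, 1500 replicates. It took n=300 (500 × 2/3 × an assumed 90% reporting) and n=600. Constant gaps of 0.2 / 0.3 / 0.4 in the group naming both reasons: planned test 29 / 60 / 85% at n=300, product-term test 5–6%. Slope higher by 0.3, crossing at mean burden: planned test about 5%, product-term test 59% (n=300) and 90% (n=600). The same slope difference meeting at zero, n=300: 89% against 58%.

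**5. Precision of a slope difference.** Under the step 3 assumptions, burden has SD √0.05 = 0.224. At n=667, categories with 25% and 30% shares hold about 167 and 200 people, so SE = (5 / 0.224) × √(1/167 + 1/200) ≈ 2.3 and the 95% half-width is about 4.6, against a common slope of 6. At n=333 (about 83 and 100 people) the half-width is about 6.5.

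**The case against.** The strongest reply is that the article asks no slope question. It compares reported types of discrimination, which is a categorical exposure, and the model estimates a categorical association at equal burden. Whether attribution says anything about health beyond the total score is a proper Aim 3 question, and a main effect answers it. That stands. It follows that the rejections under a constant gap are not false positives for that narrower question; they mislead only if read as a difference in impact. The Introduction, however, frames the matter as whether impacts depend on attribution and announces a comparison of correlations with health. No attribution-specific correlation is estimated.

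Three further points stand. If zero discrimination does no harm, the lines meet at zero burden, and there the planned test is the more powerful one; the missed case needs lines that cross near mean burden. A product term does not remove confounding and supplies no unexposed group. Interaction also depends on scale, so the linear and logistic versions test different nulls. These are reasons to add the term rather than substitute it.

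A reader might infer more than the article supports:

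- That the attribution-free decision hangs on this analysis alone. Aim 3 also compares burden across the three versions, measures concordance of attributions with social position, analyses interviews and integrates the results.
- That the model repeats the loss of dose-response information that the Introduction criticises. That criticism concerns analyses that dichotomise discrimination or count attributions; this model retains total burden.

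It can also be said that a condensed article may leave product terms to a fuller plan. But here target, predictor, adjuster and population are all stated, and the mismatch lies between them.

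**Conclusion.** The point holds as a mismatch between the question and the stated models. Their attribution coefficients are adjusted mean differences in distress, or in the log-odds of fair or poor health, at equal burden. They are valid for that, but they do not separate a level difference from a difference in the burden–health relation. Under the assumptions above, quite different truths give the same coefficient and about 80% rejection, and a large slope difference that crosses at mean burden is found at no more than the 5% error rate.

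The article does not support the broader claim that the planned test generally lacks power: it detects slope differences well when the lines meet at zero burden. The algebra rests only on the stated model, plus equal burden distributions for the simple formula. The percentages rest on assumed shares, slopes, residual SD and reporting rate, and cover the linear model only.

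**What to change.** In Aim 3, Quantitative Analysis:

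1. Keep the main-effect models and describe their coefficients as differences in mean distress, or in the odds of fair or poor health, at equal total burden.
2. Alongside them, fit the same linear and logistic models with the product of centred burden and attribution category. Report category-specific slopes, or odds ratios per SD of burden, with 95% confidence intervals.
3. State that the two results are read together: a gap with similar slopes is a level difference whose origin the data cannot settle; only differing slopes speak to a different burden–health relation.

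The cost is analysis wording and one product term per model, with no new data. It adds 3 measures × 2 outcomes × 2 populations (SGM and women) = 12 product-term tests, or 24 if Black and Latino/a/x respondents are modelled separately. With about 300 to 667 respondents the slope differences will be imprecise, so conclusions should come from the intervals and not from significance alone. A non-significant product term should not be reported as equal impact. The text should also say that the interaction is scale-dependent and does not remove confounding.

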#### Demographics

Age, sex assigned at birth, current gender identity, race, ethnicity, immigration history, education, income, sexual orientation, geographic region, and community size (eg, urban and rural) data will be collected.

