### Sample Size

For cognitive interviews, our sample size exceeds qualitative research guidelines for achieving data saturation—the number of interviews by which no new relevant themes are identified (eg, up to 25 participants) [82,83]. The quantitative survey sample sizes were determined based on sample size requirements for multigroup CFA, which has the greatest sample size requirement among the planned analyses. Simulation studies show that 200 respondents per group is the minimum number required to have ≥80% power to detect measurement invariance via changes of ≥0.002 in the comparative fit index [75]. Therefore, we will recruit 250 per race and ethnicity*SGM*gender stratum in English (n=3000); the Spanish-language sample (n=500) will allow for mCFA by language as well as by SGM status, race, or gender. All other planned quantitative analyses have smaller sample size requirements.

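### The Aim 3 attribution-health regressions name total burden as their only adjustment although attribution is self-selected, and the claim that the survey is large enough for them is unsupported for small differences

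*Protocol article*

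**What the plan says.** In Aim 3, Quantitative Analysis, respondents from the attributed versions who report any discrimination are sorted into four categories, which are related to the outcome: "race and/or ethnicity, sexuality and/or gender, both, or other attributions only) and psychological distress, adjusting for total discrimination burden". Self-rated health is handled in a similar way by logistic regression. The models are run for each InDI measure among Black and Latino/a/x SGM. A parallel set among Black and Latino/a/x women uses race or ethnicity, gender, both, or other. No demographic covariate and no term for attribution format is named.

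The Demographics section lists what is available: "Age, sex assigned at birth, current gender identity, race, ethnicity, immigration history, education, income, sexual orientation", and more. Aim 2 names six such variables as covariates, but only for the MIMIC models.

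The Intersectional Discrimination Index section under Methods says of the English survey that "we will use the block-randomization feature in Qualtrics to implement a split-ballot design", in which "1000 participants will receive each of the unattributed, item-level attributed, or overall attributed versions of the InDI". The Spanish sample receives only the unattributed version.

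The Sample Size section bases the survey on multigroup CFA ("200 respondents per group is the minimum number required to have ≥80% power to detect measurement invariance") and adds: "All other planned quantitative analyses have smaller sample size requirements".

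**The concern.** Survey version is randomised; attribution category is not. A respondent's age, schooling, income or nativity may influence whether mistreatment is put down to race, to sexuality, or to both, and may also influence distress at a given burden. Adjusting for burden alone leaves that path open.

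The women's models are the clearest case. SGM status varies within them by design. A woman who attributes mistreatment only to her sexuality falls into the *other* category, so SGM status plausibly drives category membership. The Introduction reports that SGM respondents perceive more discrimination and that discrimination is associated with distress.

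These regressions bear on whether the health impact of discrimination depends on its attribution, which the article gives as the basis for the attribution-free design. Residual confounding could create a difference. Wide intervals could hide one, and the absence of a significant difference might then be taken as support for leaving attributions out.

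**Working it through.** **1. The plan's own figure.** The design has "the 12 intersectional race and ethnicity*SGM*gender sample strata", and "we will recruit 250 per race and ethnicity*SGM*gender stratum in English (n=3000". 3 racial or ethnic groups × 2 SGM levels × 2 genders = 12 strata, and 12 × 250 = 3000. The figure reproduces. The minimum of 200 per group comes from a cited simulation that is not shown.

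**2. How many respondents the regressions can use.**
- Attributed versions: 2 of 3, or 2000 of 3000.
- SGM in one racial or ethnic group: 2000 × 1/3 × 1/2 = 333.
- Black and Latino/a/x SGM pooled: 2 × 333.3 = 667.
- Women in one group: also 2000 × 1/3 × 1/2 = 333, of whom about 167 are SGM and 167 are not.

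The text can be read as separate models by group or by measure, so both readings are computed.

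**3. Minimum detectable pairwise difference.** The plan gives no effect size or alpha for this analysis. Assumed: 80% power, two-sided 0.05, residual SD of 1. Then MDE = 2.80 × √(1/n₁ + 1/n₂).
- One group, all reporting, equal categories: 333/4 = 83 each; 2.80 × √(2/83) = 0.43 SD.
- Pooled, same assumptions: 667/4 = 167 each; 2.80 × √(2/167) = 0.31 SD.
- Range for race versus sexuality, with 60–100% reporting and splits of 25/25/25/25, 40/15/35/10 or 50/10/30/10 (race/sexuality/both/other): 0.43–0.69 SD in one group, 0.31–0.49 SD pooled.
- Two large categories can do better. Race versus both, under the unequal splits with full reporting, gives 0.35–0.36 SD in one group and 0.25 SD pooled. Contrasts with the smaller categories are then worse.

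Needed per category, n = 2 × (2.80/d)²: 63 for d = 0.5, 175 for d = 0.3, 393 for d = 0.2 (z-values unrounded). With equal categories, 83 or 167 is enough for 0.5 SD but not for 0.3 SD.

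For self-rated health, assuming 20% versus 30% fair or poor, 294 per category are needed; power is 32% at 83 and 56% at 167.

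**4. Size of the confounding.** The documents give no strengths, so any figure is illustrative. Two simulations with a true attribution effect of zero and one omitted covariate were run.
- One gave a coefficient of 0.13 SD, which fell to 0.00 once the covariate was included.
- The other assumed that 1 SD of the covariate shifts the log-odds of an SGM attribution by 0.6 and distress by 0.5 residual SD. It gave about 0.18 SD.

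The bias is roughly proportional to the product of the two strengths. Halving one takes 0.18 to about 0.09; halving both takes it to about 0.045; it vanishes if either is zero.

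**5. Whether format confounds.** With randomised format and no true effect, the bias without a format term was:

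| What format shifts | Bias (SD) |
|---|---|
| Attribution only | 0.00 |
| Attribution, and burden by 0.2 SD | −0.01 |
| Attribution, and distress by 0.1 SD | 0.02 |

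A format term removed the last two. In the demographic scenario, a format term alone left the bias at 0.13.

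**The case against.** The strongest reply on adjustment is that this is a journal article. It names burden but never says that nothing else enters, and Table 1 calls the models multivariable. A fuller plan may list more covariates. Restriction to SGM of colour also limits confounding by SGM status and race in the main models. The restriction argument stands for those two variables, but not for age, gender, socioeconomic position or nativity, and not for SGM status in the women's models. The condensation argument carries less weight, because the same article spells out demographic covariates for MIMIC and here names burden only.

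Three stronger readings are tempting and should not be drawn:
- **That pooling the two attributed versions confounds the result by format.** Format is block-randomised, and the bias in step 5 is at most about 0.02 SD. The supportable point is comparability: item-by-item and overall questions may not sort people into the same four categories. Pooling without distinction is itself only the natural reading of the text.
- **That the sample size sentence is false.** It states no target effect for Aim 3. With equal categories and full reporting, 83 per category exceeds the 63 needed for 0.5 SD.
- **That these regressions alone decide Aim 3.** They are one strand of a mixed-methods design that also uses burden comparisons, concordance and interviews, merged in a joint display. No rule turns a null regression into a decision.

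It is also fair to say that a heavy model would worsen precision. Within one group, assuming 20% fair or poor health and 60–100% reporting, the logistic model has 333 × 0.6 × 0.2 = 40 to 333 × 0.2 = 67 events.

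**Conclusion.** The concern holds in a limited form. As written, the regressions treat a self-selected exposure with one named adjustment, although plausible common causes are collected. In the women's models SGM status varies about 50:50 and is unadjusted. The direction and size of the bias are unknown; 0.13–0.18 SD is an illustration under chosen strengths, and weaker ones give less. A particular false-positive rate cannot be claimed.

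The sufficiency sentence is unsupported for these models rather than contradicted. With full reporting and equal categories they can detect about 0.43 SD within a group or 0.31 SD pooled. Lower reporting raises these figures, as do unequal splits for any contrast that involves a small category. The sentence is reasonable for 0.5 SD, but not in general for 0.3 SD or less. Format raises a question of comparable categories, not of confounding.

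**What to change.** - Adjust the linear models for age, gender, education, income and nativity. Add SGM status in the women's models, and race and ethnicity wherever groups are pooled.
- Keep the set short in the logistic models. Three category terms, burden, five single-term covariates and format make 10 slopes, against perhaps 40–67 events in one group.
- Add a main-effect term for attribution format and show estimates by format descriptively. A category-by-format interaction need not be required: one group in one format has 167 respondents, about 42 per category, and an MDE of 0.61 SD.
- Limit the Sample Size sentence by giving the minimum detectable differences above with their assumptions.
- Report confidence intervals for the category contrasts, and state that a non-significant result will not be read as evidence that attribution does not matter.

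No new data are needed. The cost is a few degrees of freedom and a less favourable statement of precision.
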